**Fig. 2 Fig2:**
[figure not shown]
Intervention screenshot examples—main subpages. Note: main subpages of the website intervention include (a) *Why be Active*, capability and motivation; (b) *How to be Active*, opportunities and skills; (c) *Be inspired*, coping role models; (d) information about the programme; and (e) contact details for enquiries

Participants will receive one telephone health coaching consultation, which will occur within 2 weeks of randomisation. The consultation session will facilitate goal setting and physical activity behaviour change, using evidence-based theoretically informed behaviour change principles. Health coaching will be provided by a tertiary-trained physiotherapist with additional training in motivational interviewing and behavioural intervention techniques, and experience in delivering telephone-based health coaching in the context of research studies.

Participants will receive either 8 email messages or 24 SMS messages depending on their preference. The messages will be similar in content and aim to support physical activity using behaviour change techniques, informed by the COM-B system model of behaviour [13] and SDT [12]. Behaviour change techniques will include providing practical tips, addressing barriers, providing motivation by social modelling and reminders of the benefits of physical activity, assisting with action planning, problem-solving and time management. These messages will also contain a link back to the *Active Women over 50* website.

### Control group

Participants randomised to the control group will be waitlisted to receive access to the *Active Women over 50* full programme after the 3-month follow-up data collection period.

### Outcomes

#### Primary outcomes

The primary outcome will be participant acceptability of the intervention and study methods. A global measure will assess whether participants would recommend participation in the study to someone else like themselves. Participants will be asked to select “yes” or “no/unsure” to the question “Would you recommend the *Active Women over 50* study to another person such as yourself?” at 3 months post-randomisation.

#### Secondary outcomes

Secondary outcomes will measure the feasibility of the study methods and intervention and the impact of the intervention. Feasibility will be evaluated with process indicators at 3 months post-randomisation using study records to measure the 1) rates of recruitment assessed by the proportion of people screened who met the inclusion criteria and proportion of eligible people who agreed to participate in the study; 2) representation of sociodemographic characteristics of participants screened and consenting to participate in the study; 3) retention of participants assessed by the number of participants who withdraw consent or participation; 4) mode by which people heard about the study; 5) completeness of outcome data assessed by accelerometer and survey questionnaire outcome data; 6) uptake of telephone health coaching consultation with the research physiotherapist, assessed by the proportion of intervention participants who make an appointment with the research physiotherapist health coach; 7) uptake of the *Active Women over 50* website resource, assessed by the proportion of intervention participants who used the website, the website content that was accessed and the intensity of website usage, measured by Google Analytics; and 8) engagement with the email messages, assessed by the proportion of intervention participants who open the automated email messages sent by secure email marketing website *Vision6* [40]. Records will be kept when different aspects of the intervention are offered, delivered and received by each participant.

Intervention impact will be measured via a questionnaire and *Actigraph GT3X+* accelerometer, as detailed below, at 3 months post-randomisation assessing 1) the average number of steps taken per day (accelerometer measured), 2) the proportion of participants taking part in at least 150 min of moderate-intensity physical activity per week or at least 75 min of vigorous-intensity physical activity per week (as recommended by the Australian Physical Activity Guidelines) [5] (accelerometer measured), 3) exercise perceptions as measured by the *Exercise Benefits and Barriers Scale* [41], 4) mood as measured with the positive and negative subscales of the *Positive and Negative Affect Schedule* [42], 5) self-reported physical activity as measured by the *International Physical Activity Questionnaire* [43], 6) physical functioning as measured by the function component of the *Late Life Function and Disability Instrument* [44], and 7) health-related quality of life as measured by the *EQ-5D-5 L* survey [45].

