### Eligibility criteria

Women are eligible for inclusion in the trial if they are aged 50 years and over, and community-dwelling residents in New South Wales, Australia. Potential participants will be excluded if they have limited English language skills, do not have access to the internet, have a medical condition that precludes participation in regular physical activity or are already sufficiently active in accordance with Australian physical activity guidelines [5].

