### Recruitment

Participants will be recruited through advertising in newsletters and websites of community organisations, university and local health districts, via the study recruitment website, www.activewomenover50.org.au, word-of-mouth and social media. Participation is cost-free and no incentives are offered for participation. Potential participants will be screened for eligibility via an online survey. Recruitment commenced 3 May 2019, and at the time of submission of this manuscript, 66 participants had been recruited, 56 randomised and 0 participants had completed follow-up measures.

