### Analysis of outcomes

Feasibility outcomes will be analysed descriptively to guide the design of a larger trial. Accelerometer data will be analysed using *ActiLife 6* software with time spent in different activity intensity levels calculated using the Troiano 2008 cut-points [47]. Acceptable wear time will be defined as at least 4 days with 10 h or more per day of valid wear time. Periods of 90 min or more of consecutive zeros (indicating non-use) will be considered as non-wear time.

Odds ratios will be calculated to assess the acceptability and feasibility of the study on the dichotomously scored primary outcome (the likelihood a participant would recommend participation in the study to someone else such as themselves) to assess the effect of group allocation on the dichotomously scored secondary outcome (proportion of people achieving physical activity in accordance with national guidelines) [5], adjusting for baseline scores. The study methods will be considered feasible if at least 80% of all participants complete follow-up measurements, or 80% of intervention participants access the intervention website or participate in the telephone health coaching session. Intervention versus control group differences in secondary outcomes, analysed with general linear models adjusting for baseline scores, will estimate effect sizes for sample size calculations for a larger trial and will provide an indication of likely intervention effect. This will be the progression criteria for proceeding to a fully powered randomised controlled trial.

A *p* value of < 0.05 will be considered statistically significant. Analyses will be pre-planned, conducted while masked to group allocation and will use an intention-to-treat approach. Analyses will be conducted using the *Stata 14* software package.

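### The only accelerometer outcome on activity intensity is a met/not-met proportion; the weekly minutes behind it are calculated but not analysed, which costs precision

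*Protocol article*

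**What the plan says.** All references are to the protocol article.

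- **Eligibility criteria** and **Recruitment**: women are excluded if they are "already sufficiently active in accordance with Australian physical activity guidelines". How this is judged is stated separately: "Potential participants will be screened for eligibility via an online survey".
- **Secondary outcomes**: seven impact outcomes are listed at 3 months. Two come from the accelerometer. The first is continuous: "the average number of steps taken per day (accelerometer measured"). The second is binary: "the proportion of participants taking part in at least 150 min of moderate-intensity physical activity per week or at least 75 min of vigorous-intensity" activity per week.
- **Data collection procedure** and **Objectively measured physical activity**: the accelerometer is worn for one 7-day period at baseline and one at 3 months.
- **Analysis of outcomes**: the software output includes "time spent in different activity intensity levels calculated using the Troiano 2008 cut-points". The binary outcome is analysed by odds ratio: "proportion of people achieving physical activity in accordance with national guidelines) [5], adjusting for baseline scores". A later sentence assigns general linear models, adjusted for baseline, to the group differences in secondary outcomes and says these will supply effect sizes for sizing the larger trial.

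Time at each intensity is thus computed at both time points, but moderate-to-vigorous minutes do not appear in the outcome list as a quantity to be compared.

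**The concern.** Two things follow from fixing intensity as a threshold proportion.

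First, precision. A woman who moves from 20 to 140 minutes a week counts the same as one who does not change, and a woman who moves from 145 to 155 counts as a full success. With 30 women per arm there is little information to spare. A planner of the larger trial who wants to size it on intensity needs a mean difference, a standard deviation and a baseline-to-follow-up correlation. An odds ratio supplies none of these.

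Second, interpretation. The trial enrols women described as insufficiently active and then reports the share who meet a guideline threshold at 3 months. It is natural to read that share as women who became sufficiently active. The entry decision comes from a survey and the outcome from a device, so some women may have been above the device threshold from the start.

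**Working it through.** **Figure to reproduce.** None. Sample size justification gives 60 women in equal arms (30 per arm) on feasibility grounds, with no effect size, standard deviation or event rate. The inputs below marked as assumed are therefore shown as ranges.

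**Step 1: information kept by the cut.** For a normal outcome cut where a fraction p lies above the threshold, the information kept for a small shift is φ(z)² / [p(1 − p)], with z the normal quantile at p.

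| Fraction meeting threshold (assumed) | Information kept | Women needed relative to continuous (1 / kept) |
|---|---|---|
| 50% | 0.637 | 1.57 |
| 30% | 0.576 | 1.74 |
| 20% | 0.490 | 2.04 |
| 10% | 0.342 | 2.92 |

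For example, at p = 0.5: φ(0)² / 0.25 = 0.159 / 0.25 = 0.637. More than half is lost only when p is below about 21%.

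**Step 2: the same loss as a trial size.** Assume a true shift of 0.5 SD, two-sided alpha 0.05 (the article gives 0.05 without sidedness) and 80% power.

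- Continuous, unadjusted: 2(1.960 + 0.842)² / 0.5² = 62.8, so 63 per arm.
- Continuous, adjusted for baseline with assumed correlation 0.6: 62.8 × (1 − 0.36) = 40.2, so 41 per arm.
- Binary, unadjusted: with control rates of 10%, 20%, 30% and 50%, the same shift gives intervention rates of 21.7%, 36.6%, 49.0% and 69.1%. The pooled two-proportion formula then needs 152, 115, 103 and 102 per arm.

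The like-for-like pair is 63 against 102 to 152. The figure of 41 includes the gain from baseline adjustment, which the binary figures do not.

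**Step 3: both analyses adjusted.** A simulation with 30 per arm gave both models the continuous baseline value. Assumptions: true shift 0.5 SD; baseline-to-3-month correlation 0.7; survey-to-accelerometer correlation 0.3; 35% of source women above the threshold. Over 2,000 simulated trials, power was 77% for the linear model and 44% for the logistic model.

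**Step 4: women already above the threshold on the device.** The Background gives 65% of women over 55 as insufficiently active. As an illustration, take 35% above the threshold on both instruments. With c defined by Φ(c) = 0.65 and correlation r between survey and accelerometer, the chance of being above on the accelerometer given below on the survey is 1 − Φ₂(c, c; r) / 0.65.

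| r (assumed) | 35% of source above | 20% of source above |
|---|---|---|
| 0.3 | 28% | 17% |
| 0.5 | 24% | 14% |
| 0.7 | 18% | 11% |
| 0.9 | 10% | 6% |

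The formula contains no time term. It describes the baseline wear week, and also the 3-month week if nothing changes. At 28%, that is about 8 of 30 women per arm (0.28 × 30 = 8.4).

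**Step 5: does this bias the comparison?** In a simulation with no effect (30 per arm, 4,000 trials, correlations as in step 3), 28% of women were above the threshold at 3 months. The baseline-adjusted logistic model rejected in 4.2% of trials against a nominal 5%.

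**The case against.** The strongest reply is that this is one of seven impact outcomes in a pilot whose primary outcome is acceptability. No power is claimed, and the numerical feasibility thresholds concern follow-up, website access and coaching. The guideline proportion is easy to communicate, and reporting minutes as well could be seen as detail for a fuller document. This stands as a limit on importance. It does not remove the point, because the article itself fixes both the form of the outcome and its model.

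A reader might also infer stronger things that the article does not support:

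- *That chance crossings produce a false effect, so a minimum change or a confirming week is needed.* The outcome is a proportion compared between randomised arms, not a within-person response. Crossings occur in both arms and dilute the contrast; step 5 shows no inflation of type I error.
- *That one measurement is cut twice at the same point.* Entry is by survey and the outcome is by device. The guideline described in the Background also covers combined moderate and vigorous activity and muscle strengthening, which the 3-month threshold as worded does not.
- *That most of the accelerometer information is lost.* Steps per day keeps its continuous form. For the intensity variable, the loss in step 1 exceeds half only below a rate of about 21%, and no rate is given.
- *That the larger trial will be sized on the odds ratio.* Analysis of outcomes gives that role to the linear models.
- *That the odds ratio adjusts for baseline met/not-met status.* The text says only baseline scores.

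**Conclusion.** The point holds as a matter of precision and interpretation, and its weight is modest. Intensity is the one accelerometer dimension without a continuous analysis, although the minutes exist at both time points and a suitable model is already planned. Under a normal model the cut keeps about 64% of the information in this variable at a 50% rate of meeting the threshold, 49% at 20% and 34% at 10%. Weekly minutes may be skewed, in which case these figures apply to a suitably transformed scale.

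The 3-month proportion should not be described as women moved from insufficient to sufficient activity, because an unknown share may already be above the threshold at baseline (6% to 28% over the ranges in step 4). The rates, correlations and the 0.5 SD shift are assumptions; the article supplies none of them apart from the 65% used for illustration. The comparison between arms remains valid. What is lost is a sharper intensity estimate for planning the larger trial.

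**What to change.** 1. In Secondary outcomes, add accelerometer-measured weekly minutes of moderate-to-vigorous activity as a continuous impact outcome.
2. In Analysis of outcomes, analyse those minutes (transformed if skewed) with the general linear model already planned, with baseline minutes as the covariate. Report the difference with its interval, the standard deviation and the baseline-to-follow-up correlation.
3. Keep the guideline proportion, but tabulate it by baseline accelerometer status within each arm, so that women already above the threshold are visible and new crossings can be set against those in the control arm.
4. State that any odds ratio for this outcome adjusts for continuous baseline minutes.

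No new data collection is needed. The cost is one more secondary analysis, and minutes are slightly less direct to communicate than a guideline proportion, which is still reported.

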**Methods:**

Sixty community-dwelling women who are insufficiently active according to national guidelines, will be recruited and randomised to 1) receive the *Active Women over 50* programme or 2) a wait-list control. *Active Women over 50* is a 3-month physical activity programme guided by behaviour change science, providing access to a website, one telephone-delivered health coaching session from a physiotherapist and 8 email or 24 SMS messages. The primary outcome is the proportion of participants at 3 months post-randomisation who would recommend participation in the programme to another person like themselves. Secondary outcomes are feasibility measures: rates of recruitment, retention, completeness of outcome data and uptake of telephone support; and intervention impact measures: accelerometer-assessed average steps/day, proportion of participants meeting national guidelines on moderate to vigorous physical activity; and questionnaire-assessed quality of life, exercise perceptions, mood, physical functioning and self-reported physical activity. Intervention participants will also complete a follow-up survey to assess impressions of the intervention and adoption of strategies for physical activity participation. Data will be analysed descriptively to guide the design of a larger trial. Between-group differences in secondary outcomes will be used to estimate effect sizes for sample size calculations for a fully powered randomised controlled trial.

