## Background

Physical inactivity is a significant but modifiable public health problem. Globally, it is associated with 5.3 million deaths [1] and has an economic cost of INT$67.5 billion per year [2]. Physical inactivity is as important a risk factor for developing chronic disease and disability as smoking and obesity [3].

There is compelling evidence of the benefits of physical activity for physical and mental health at all ages [3] and maintenance of independence in older age [4]. Regular physical activity can prevent or help manage some health conditions and has been reported to delay disability by up to 15 years in older women [4]. The national guidelines for physical activity recommend Australian adults to accumulate 150 to 300 min of moderate-intensity or 75 to 150 min of vigorous-intensity physical activity, or an equivalent combination of both moderate and vigorous activities each week, and to do muscle-strengthening activities on at least 2 days each week [5]. Achieving the national guidelines for physical activity in middle age has longevity benefits regardless of baseline physical activity [6].

Physical activity participation is sub-optimal in women in their middle age and very low in older women. Sixty-five per cent of women over the age of 55 years and 80% of women over the age of 75 years do not participate in sufficient regular physical activity to gain health benefits [7]. While some women become more physically active with retirement [8] this may be too late to prevent disability in older age. By 2023, Australian women will be retiring at an older age with access to the senior pension age increasing to 67 years [9]. Commencement of sufficient regular physical activity before retirement therefore needs to be a priority and maintained in the long term to promote independent and healthy ageing.

Barriers to physical activity participation for women are unique. The 2014 national survey showed that women have higher sedentary time and greater carer responsibilities than men [10, 11]. These barriers, coupled with the demands of paid work and low confidence for participating in physical activity in the absence of a previous habit, place women in their middle-age years particularly at risk of being insufficiently physically active to maintain good health. This population would benefit from a targeted and supported evidence-based approach to increase their physical activity in a way which is achievable and sustainable.

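### The accelerometer outcome for meeting the activity guideline leaves out the combined moderate-plus-vigorous route, so it can only under-count attainment of the aerobic guideline

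*Protocol article*

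**What the plan says.** The Background section sets out the national guideline, citing reference 5. The first two aerobic routes are to "accumulate 150 to 300 min of moderate-intensity or 75 to 150 min of vigorous-intensity physical activity". The section then allows a third route, in these words: "or an equivalent combination of both moderate and vigorous activities each week". Apart from the aerobic routes, the guideline as described there has a strength component, covered by advice on muscle-strengthening work.

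The Secondary outcomes section defines the second intervention-impact measure, taken by accelerometer, as the proportion doing "at least 150 min of moderate-intensity physical activity per week or at least 75 min of vigorous-intensity physical activity per week". It presents this as the guideline's recommendation, with the same reference. The combined route does not appear.

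Elsewhere the outcome carries a guideline label. The abstract calls it the "proportion of participants meeting national guidelines on moderate to vigorous physical activity". Analysis of outcomes calls it the "proportion of people achieving physical activity in accordance with national guidelines", to be compared between groups by an odds ratio adjusted for baseline. No section adds the combined route to the definition.

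**The concern.** The two-route rule is an explicit numerical definition, and it disagrees with the guideline it claims to apply. An analyst who codes it literally will score some women as not meeting a guideline whose aerobic part they do meet. Those affected have a mix of moderate and vigorous minutes in which neither is sufficient alone.

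What is at stake is the attainment proportion. The pilot exists partly to supply estimates for the sample size of a full trial (Sample size justification; Analysis of outcomes). A proportion that is too low for the guideline named would be carried forward under the wrong label.

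**Working it through.** The protocol gives no figure to reproduce: 60 women are planned, without power inputs or expected rates. The check is therefore a comparison of two rules, followed by an illustration of size.

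**Inputs.** M and V are weekly moderate and vigorous minutes. The single-route minimums are 150 and 75 (Background; Secondary outcomes). The protocol does not define an equivalent combination. Its lower limits (150 : 75) and upper limits (300 : 150) both imply that one vigorous minute counts as two moderate minutes.

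- Rule A (Secondary outcomes): M ≥ 150 or V ≥ 75.
- Rule B (Background, aerobic part): M + 2V ≥ 150. This contains both single routes, since 150 + 2 × 0 = 150 and 0 + 2 × 75 = 150.

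**Individual cases**

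| M | V | M + 2V | Rule A | Rule B |
|---|---|---|---|---|
| 100 | 30 | 160 | fails | meets |
| 140 | 10 | 160 | fails | meets |
| 80 | 40 | 160 | fails | meets |
| 149 | 74 | 297 | fails | meets |
| 150 | 0 | 150 | meets | meets |
| 0 | 75 | 150 | meets | meets |

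The fourth row is an extreme case: 297/150 = 1.98 times the minimum, still scored as a failure.

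**Direction.** Any pair that passes A passes B. On whole minutes (M from 0 to 300, V from 0 to 150), no pair passes A and fails B. The reverse holds for 5,550 pairs: for each V from 0 to 74 there are 2V values of M from 150 − 2V to 149, and the sum of 2V is 74 × 75 = 5,550. This counts combinations and is not a prevalence. It shows that the error has one sign.

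**Size, under assumptions not in the protocol.** Let M be lognormal with median 110 and log-SD 0.6. Let a share s of women do any vigorous activity, with lognormal V of log-SD 0.6, independent of M. Then P(M ≥ 150) = 1 − Φ(ln(150/110)/0.6) = 1 − Φ(0.517) = 0.303. Rule A attainment is 1 − (1 − 0.303)(1 − s·P(V ≥ 75)). Rule B attainment is 0.303(1 − s) + s·P(M + 2V ≥ 150), by numerical integration.

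| Share with any vigorous activity | Median V (min) | Rule A | Rule B | Under-count (points) |
|---|---|---|---|---|
| 10% | 10 | 30.3% | 31.4% | 1.1 |
| 20% | 15 | 30.3% | 33.9% | 3.6 |
| 30% | 20 | 30.6% | 37.7% | 7.2 |
| 40% | 30 | 32.0% | 45.0% | 13.0 |

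With 60/2 = 30 women per arm, the ends of this range are 30 × 0.011 ≈ 0.3 and 30 × 0.130 ≈ 3.9 women per arm.

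**Between-arm effect, same model with vigorous log-SD 0.8**

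- The programme raises only the moderate median, from 110 to 140. With 20% doing vigorous activity at a median of 15 minutes, Rule A goes from 30.57% to 45.66% (odds ratio 1.91) and Rule B from 34.36% to 49.30% (1.86). With 40% at 30 minutes, Rule A goes from 33.78% to 48.17% (1.82) and Rule B from 45.20% to 58.47% (1.71).
- The programme adds only vigorous activity, from 20% at 15 minutes to 30% at 20 minutes. Rule A goes from 30.57% to 31.29% (1.03) and Rule B from 34.36% to 38.33% (1.19).

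The odds ratio as written is therefore larger than the guideline-based one in the first case and smaller in the second.

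**The case against.** The strongest reply is that little depends on this. It is one of seven impact measures in a feasibility pilot whose primary outcome is acceptability, and the numerical 80% feasibility thresholds do not use it. The trial excludes sufficiently active women, so vigorous activity may be rare, and a gap of 1 to 4 points is about one woman per arm or fewer. Minutes by intensity are derived anyway, so a combined count can still be produced at analysis. All of this stands, and it limits the weight of the point. It does not reconcile the definition with the guideline it cites.

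It can also be said that the abstract's moderate-to-vigorous wording shows a combined total was meant. The operative definition does not say so, and the abstract gives no weighting. An unweighted sum of at least 150 would not match the guideline either: 75 vigorous minutes alone would fail, and so would 100 + 30 = 130.

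A reader might infer three stronger things that the protocol does not support:

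- **That the rule biases the comparison against the programme.** This would need the programme to add vigorous minutes in particular. Nothing in the protocol says it will, and its messages stress starting small and building up gradually. If only moderate minutes rise, the odds ratio as written is slightly larger in these scenarios.
- **That women above 150 minutes who do no strength work are enrolled as successes at baseline.** Eligibility criteria excludes women "already sufficiently active in accordance with Australian physical activity guidelines", and screening is by online survey. How sufficiency is scored, and whether strength work is asked about, is not shown.
- **That misclassified women meet the whole guideline.** They meet its aerobic part. The guideline as quoted also includes muscle strengthening, which this outcome does not measure.

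**Conclusion.** The point holds in a limited form. The outcome definition contradicts the guideline as the protocol quotes it, and women who reach the aerobic minimum only through a mix are scored as not meeting it. The one-way under-count is certain in sign, given the 2:1 weighting implied by the protocol's thresholds, and can affect both arms.

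Its size is not computable from the document. The range of about 1 to 13 points rests wholly on assumed activity distributions, and the upper end needs 40% of these women to do vigorous activity at a median of 30 minutes a week. The sign of any between-arm bias is open. The consequence is confined to a secondary outcome and to the planning estimate taken from it. It is worth correcting because the correction is nearly free.

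**What to change.** In Secondary outcomes, define attainment as weekly moderate minutes + 2 × weekly vigorous minutes ≥ 150, and state that the 2:1 weight comes from the guideline's own limits. Label the outcome the aerobic component of the guidelines there, in the abstract and in Analysis of outcomes, since muscle strengthening is not captured. If the two-route rule is deliberately kept, stop describing it as meeting the guideline.

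The cost is one derivation line and a relabel. Analysis of outcomes already plans to derive time at each intensity level, so no new data are needed. The Recruitment section reports that no participant had completed follow-up when the article was submitted, so a change at that point could have been made without sight of outcomes. The downside is slightly higher attainment in both arms, including control.
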